### Statistical methods

#### Machine learning algorithms

The performance of the entire machine learning algorithm (described in ‘data analysis’ above) will be assessed using cross-validation, a standard approach that consists of splitting the data into several sub-sets (‘folds’) while ensuring that the distribution of the data in each subset is similar. Some subsets are used for feature selection and classifier training, while others are used for computing an unbiased estimate of the specificity and sensitivity of the classifiers. Each infant will be assigned to one subset of the data, such that data from the same infant will not be used both for training and testing. We will use stratified 5-fold cross-validation, which ensures that reliable estimates of the sensitivity, specificity, and variance of the predictors can be obtained. ROC curves reflecting the sensitivity and specificity trade-off will be produced and used to analytically determine the best trade-off from the point of view of clinical practice [57].

The machine learning system will produce a binary prediction of whether a baby will succeed or fail extubation. However, for use in the clinical setting, a confidence measure in the classification would be necessary. To this end, we will use a method for estimating conditional probabilities for SVM, proposed by Platt [71], and efficiently implemented by Lin et al. [72]. This approach works on top of an existing support vector machine to produce an estimate of the probability that each example belongs to the class of interest. Our objective is to use these estimates to classify infants into 3 classes: (i) **FAILURE**: infants assigned to the failure group with high confidence; (ii) **SUCCESS**, infants assigned to the success group with high confidence; (iii) **UNCERTAIN**, infants assigned to either the success or fail groups with low confidence. Where the boundary should lie between high and low probability will depend upon the relative cost associated with a false negative (resulting in the extubation of an infant who will fail) versus that of a false positive (extending the period of ventilation for an infant who would otherwise be extubated). Given the nature of the experimental design (i.e. infants are only studied when deemed ready for extubation) we anticipate that the clinical implementation of our methods would involve delaying extubation for infants predicted to fail. We will evaluate performance based on two measures for the FAILURE class, the identification rate (IR) and the false discovery rate (FDR), defined as:$$ IR=\frac{NF_{fc}}{NF_T};\kern0.39em  FDR=\frac{NS_{fc}}{NS_{fc}+{NF}_{fc}} $$

*where NF*
_*T*_ = total number of failures

*NF*
_*fc*_ = number of failures assigned to FAILURE class

*NS*
_*fc*_ = number of successes assigned to FAILURE class.

Bootstrap methods will be applied to our data to estimate the threshold value that provides the largest value for IR with an acceptable FDR.

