### Extubation

There is no consensus on when an extremely preterm infant should be extubated. Thus, prior to initiation of the study, we proposed the following guidelines to consider a patient ‘ready’ for extubation: For infants <1000 g - mean airway pressure (MAP) ≤ 7 cmH_2_O and fraction of inspired oxygen (FiO_2_) ≤ 0.3; For infants ≥1000 g - MAP ≤8 cmH_2_O and FiO_2_ ≤ 0.3. Nevertheless, all decisions regarding weaning, determination of extubation readiness and post-extubation management are ultimately made by the responsible physician. In general, all units have adopted SpO_2_ target ranges according to their respective institutional guidelines and have been practicing a permissive hypercapnia ventilator strategy. Caffeine therapy is commonly administered prior to extubation as part of standard care. Infants typically receive post-extubation respiratory support in the form of either nasal CPAP or non-synchronized nasal intermittent positive pressure ventilation (NIPPV), at the discretion of the attending physician. These are the two most frequently used and best regarded support modalities [22, 23]. However, since design of the study and beginning of patient recruitment, we have observed that an increasing number of infants are being extubated to heated humidified high flow nasal cannula (HHHFNC) therapy. This modality is the subject of ongoing investigations, and some uncertainty remains regarding its effectiveness in preventing extubation failures in the extremely preterm population when compared to CPAP or NIPPV [56]. This has led to adjustment of the final sample size in order to account for this new practice (see ‘sample size calculation’ below).

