**Fig. 2 Fig2:**
[figure not shown]
Representative example of a cardiorespiratory recording from a preterm infant. The signals displayed, from top to bottom, are: electrocardiogram, rib cage movements, abdominal movements, sum of rib cage and abdominal movements, oxygen saturation and photoplethysmography

Data is acquired from each infant while quiet, stable and in supine position, during 2 continuous recording periods immediately preceding extubation:A 60-min period while the infant receives any mode of conventional MV. These data will be used to characterize the HRV properties of the infant prior to extubation. However, this data may not be suitable for characterizing RV, since the respiratory pattern is still influenced by the ventilator.A 5-min period will be used to record the respiratory parameters. During this time, the ventilation will be switched to endotracheal CPAP at the same positive end-expiratory pressure level used during the first recording period, so that the cardiorespiratory patterns are controlled by the infant.

II. *Acquisition of clinical data.*

The key clinical variables recorded for each infant are summarized in Table 2, and the following respiratory outcomes are recorded while the infant is hospitalized in the NICU:

**Table 2 Tab2:** Clinical variables to be collected for infants enrolled in the study

Antenatal and maternal variables	Mother age, parity, complications during pregnancy, maternal medications, intra-uterine growth restriction, mode of delivery, multiple birth, use of antenatal steroids, rupture of membranes, use of antibiotics during labor, histological chorioamnionitis.
Infant characteristics pre-extubation	Gender, birth weight, gestational age, Apgar scores (1, 5 and 10 min), cord blood gases, use of surfactant (age, dose), use of antibiotics and caffeine administration prior to extubation (age and dose).
Infant characteristics at time of extubation	Weight at extubation, age and post-conceptional age at extubation, ventilator mode, peak inflation pressure, positive end-expiratory pressure, mean airway pressure, tidal volume, set inspiratory time, ventilator rate, fraction of inspired oxygen (FiO_2_), oxygen saturation and blood gas
Infant characteristics post-extubation	Type of non-invasive respiratory support, interface used, settings, FiO_2_ and blood gas
Primary extubation outcome	Fulfilling extubation failure criteria within 72 h from extubation

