### Sample size

The machine learning methods that will be used for this study have built-in mechanisms to guard against over-fitting the data (i.e., representing the training examples perfectly but having weak predictive power on new data). Consequently, traditional statistical approaches for determining sample size do not apply [65]. Therefore, sample size was estimated by applying a methodology proposed by Obuchowski and McClish and detailed by Zhou et al. [66, 67]. This method relies on estimating the prevalence of the disease of interest in the study population, estimating the variance of the receiver operating characteristics (ROC) curve based on a pilot study, and picking a required precision for the area under the curve (AUC). The prevalence of extubation failure was estimated conservatively to be 20%, based on both a review of the literature and the clinical collaborators’ experience. The variance in the AUC was then estimated by applying bootstrap methods to the data acquired in our pilot study. Using these values and an AUC precision of 0.1 led to an estimated sample size of 170 babies. This sample size would provide a minimum of 5 failure cases in each fold when performing 5-fold cross-validation, thereby ensuring a reliable measurement of generalization power [68]. Nevertheless, in the face of changing practice with the increasing use of HHHFNC post-extubation, and the uncertainty related to its impact on extubation failure rates in this population, the sample size was conservatively increased to 250 patients. As for the prospective validation of APEX, the sample size of 50 infants has been chosen large enough to demonstrate the anticipated benefits and feasibility of the predictor.

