The study also has some potential limitations. Firstly, all decisions pertaining to weaning from MV, extubation, post-extubation respiratory support and reintubation are made by the responsible physician. This adds significant practice variability and a greater number of confounding factors when developing the prediction model. However, we believe that the pragmatic nature of the study makes it more reflective of clinical reality and therefore more generalizable to the real world. Besides, this concern was addressed in the derivation of the large sample size of patients. Secondly, it is important to note that the prediction model will be developed for infants who were deemed “clinically ready” for extubation by the responsible physician. This results in test-referral bias, whereby only infants pre-selected by the attending physician (based on their own personal bias of extubation readiness) are subjected to the test. Naturally, this leads to a selection of more babies with successful extubation and fewer babies with failed extubation, thereby overestimating sensitivity and underestimating specificity. Therefore, the prediction tool will only be valid in that context and cannot be generalized for all situations, until further validation [73, 74]. Lastly, it is currently unclear which criteria and time frame used to define extubation failure have the most clinical relevance for extremely preterm infants. A recent systematic review of the literature addressed this problem by evaluating extubation failure rates (defined as the need for reintubation) as a function of the time frame used. Amongst infants with BW < 1000 g, cumulative reintubation rates continued to increase up to 7 days post-extubation, with no sign of plateau [13]. Results of this review indicated that a time frame of 72 h could underestimate the true failure rate, and recommended using longer windows of observation in these infants. Although we have defined the primary outcome (extubation failure) as the fulfillment of pre-specified criteria within 72 h from extubation, we are also prospectively evaluating extubation failure using criteria up to 14 days post-extubation, as well as the need for reintubation until discharge.

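### Folds keep only the infant whole, so siblings can straddle training and test sets; performance in a new NICU is untested, and the sample size does not address practice variation as the Discussion says.

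*Protocol article*

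**What the plan says.** All references are to the protocol article.

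- **Statistical methods, Machine learning algorithms.** Data are split into folds "while ensuring that the distribution of the data in each subset is similar". The unit kept whole is the infant: "Each infant will be assigned to one subset of the data, such that data from the same infant will not be used" on both sides of a split. The scheme is fixed: "We will use stratified 5-fold cross-validation". The held-out folds are said to serve for "computing an unbiased estimate of the specificity and sensitivity of the classifiers".
- **Eligibility criteria and Table 1.** Nothing excludes siblings. Table 2 records "intra-uterine growth restriction, mode of delivery, multiple birth, use of antenatal steroids" along with other maternal items such as age, parity and histological chorioamnionitis. Under Feature Detection, the collected clinical variables go through the same selection as the signal metrics, so these items are candidate predictors.
- **Study setting and Extubation.** Five NICUs take part, two of which merged in May 2015. On oxygen targets, "all units have adopted SpO_2_ target ranges according to their respective institutional guidelines".
- **Prospective validation of APEX.** The 50 further infants are recruited and followed as in the main study. No held-out site is named.
- **Sample size.** The inputs are 20% failure prevalence, a pilot AUC variance and a precision: "Using these values and an AUC precision of 0.1 led to an estimated sample size of 170 babies". The rise to 250 is put down to the growing use of high-flow nasal cannula (HHHFNC).
- **Discussion.** Physician-led weaning, extubation, support and reintubation are acknowledged as sources of practice variability and confounding, followed by: "Besides, this concern was addressed in the derivation of the large sample size of patients".

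**The concern.** Cross-validation is unbiased for new infants only if the test infants are independent of the training infants. Siblings share a mother, a unit and a period of care, so a fold rule that protects only against reuse of the same infant leaves a dependence that the word unbiased denies.

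The site question concerns what the estimate is for. If every unit contributes to every fold, the classifier is always tested on units it has already seen. That answers how it performs in these NICUs, not how it performs elsewhere. The article nevertheless presents the pragmatic, multicenter design as making the study more generalizable.

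The Discussion sentence matters because it closes the question. A reader who accepts that practice variation was handled through the sample size will not look for a between-site analysis. The predictor is meant eventually to support delaying extubation, so the limits of its evidence should be stated correctly.

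**Working it through.** **1. The plan's own sample size.** The bootstrap variance is not printed, so 170 cannot be reproduced strictly, but it can be reached. The Obuchowski-McClish binormal variance is V = 0.0099 × exp(−A²/2) × [(5A² + 8) + (A² + 8)/R], with A = 1.414 × z(AUC). At 20% prevalence R = 4. The number of failures is 1.96² × V / 0.1², rounded up, and N is five times that.

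| Assumed AUC | V | Failures | N |
|---|---|---|---|
| 0.775 | 0.0895 | 34.4, so 35 | 175 |
| 0.79 | 0.0870 | 33.4, so 34 | 170 |
| 0.80 | 0.0850 | 32.7, so 33 | 165 |

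The fold statement also holds: 170 × 0.20 / 5 = 6.8 failures per fold, and 250 × 0.20 / 5 = 10, against the stated minimum of 5. The figures are not at fault. What matters is that the inputs are prevalence, AUC variance and precision only. No term stands for site, clustering or practice, and no calculation is shown for the step from 170 to 250.

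**2. How often siblings are separated.** With five equal folds assigned by infant, a twin pair falls in different folds with probability 1 − 1/5 = 0.80. A pair straddles any one given split with probability 2 × 0.2 × 0.8 = 0.32. The share of multiples is not stated; assume 10%, 20% or 30% of 250 infants, in twin pairs.

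| Pairs | Expected straddling per split | P(at least one in a given split) |
|---|---|---|
| 12 | 0.32 × 12 = 3.8 | 1 − 0.68¹² = 0.990 |
| 25 | 0.32 × 25 = 8.0 | 1 − 0.68²⁵ = 0.9999 |
| 38 | 0.32 × 38 = 12.2 | above 0.9999 |

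Some separation is therefore near-certain, although any single separated pair affects only two of the five splits.

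**3. Size of the sibling effect.** Two simulations bound it; all correlations are assumptions.

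- Uninformative features, 20–30% of infants in twin pairs, within-pair feature correlation 0.6, latent outcome correlation 0.3–0.5: AUC 0.509–0.516 with infant folds and 0.497–0.501 with mother folds, a gap of about 0.01 to 0.02.
- Informative features (250 infants, 17 features, kernel classifier, 200 runs per setting), 10–30% of infants in twin pairs: infant folds exceed family folds by 0.002 to 0.006. With no twins at all the same comparison gave 0.684 against 0.679, a gap of 0.005, so this is noise.

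For scale, the 95% half-width of the AUC with 50 failures at AUC 0.80 is 1.96 × √(0.0850/50) = 0.08.

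**4. Size of the site effect.** Site is not a variable in Table 2. It can enter only through proxies such as ventilator mode, settings, support type and interface. An upper illustration is the AUC of site identity alone, for five equal sites with evenly spaced failure rates averaging 20%: the sum over sites of P(site | failure) × [P(lower-risk site | success) + ½ P(same site | success)]. For rates of 10, 15, 20, 25 and 30% this is 0.10 × 0.1125 + 0.15 × 0.33125 + 0.20 × 0.5375 + 0.25 × 0.73125 + 0.30 × 0.9125 = 0.625. Optimism is better judged by adding fully known site risk to a binormal marker with AUC 0.80.

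| Assumed site rates | Site alone | Marker 0.80 plus site |
|---|---|---|
| 15–25% | 0.5625 | 0.804 |
| 10–30% | 0.625 | 0.817 |
| 5–35% | 0.6875 | 0.838 |

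In the 250-infant simulation with five sites, infant-fold against leave-one-site-out AUC was 0.665 and 0.665, 0.669 and 0.657, 0.689 and 0.659, and 0.692 and 0.646 as the assumed site shifts grew. The gap is 0.00 to 0.05. Part of it arises because an AUC computed within one held-out site cannot draw on risk differences between sites.

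**5. The Discussion against the Sample size section.** The Discussion lists four sources of practice variation. The sample-size text takes up one, post-extubation support, and only as uncertainty about the failure rate. Extra infants from the same units narrow the interval; they leave confounding by unit or physician where it was.

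**The case against.** The case against is substantial, and much of it stands.

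- **Sibling bias is hardly visible.** At 0.00 to 0.02 it is well inside the planned precision of 0.1. This stands; grouping by mother is good hygiene and does not rescue a badly wrong estimate.
- **Sites on both sides of a split are normal.** This stands. A reader might infer that the cross-validated estimate is seriously inflated by site. The documents do not support that: for new infants in the participating NICUs the design is appropriate, site is not a listed feature, and the site-alone AUCs are ceilings, not estimates of optimism.
- **The outcome is partly protected from local practice.** The primary outcome uses fixed oxygen, blood-gas and apnea criteria, and reintubation is secondary. A reader might infer that unit-specific oxygen targets drive the FiO2 criterion. The text says that units follow their own guidelines; it does not say how far the targets differ or that they move the criterion, which itself fixes one SpO2 level for all sites.
- **Quality control and prospective validation exist.** Acquisition is standardised, variables are compared between sites, and 50 further infants are tested with a frozen, concealed classifier. These help, but the between-site comparison is for data quality, and the 50 infants are recruited as before.
- **The Discussion already limits generalization until further validation.** It does, but on account of physicians' preselection of infants, not of site.
- **Leave-one-site-out could be left to an analysis plan.** Its absence alone would be no finding. It is proposed because the article makes positive claims, unbiasedness and the handling of practice variation, that its stated method does not support.

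**Conclusion.** The point holds in a limited form. The fold rule does not deliver the independence that the word unbiased requires, because siblings are eligible and some pairs will almost certainly be split. The consequence is small. Cross-validation within the five units is valid for those units but gives no evidence about a new NICU, where AUC could be lower by about 0.00 to 0.05. The Discussion sentence is wrong as written, since the derivation in the Sample size section contains nothing that addresses practice variation apart from an uncalculated allowance for one change in support mode.

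The sizes rest on assumed multiple-birth shares, within-pair correlations, site failure rates and feature shifts, none of which the article gives. The faults in the fold rule and in the Discussion sentence do not depend on them. Neither 170 nor 250 is shown to be arithmetically wrong.

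**What to change.** 1. Assign folds by mother, so that siblings stay together, and keep the stratification and the five folds.
2. Beside the stratified 5-fold estimate, report leave-one-site-out AUC, IR and FDR as a secondary check, treating the merged units as one site.
3. Replace the Discussion sentence with a statement that the sample size does not address between-site or practice variation and that performance in new NICUs is untested.

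The cost is analysis code and a text edit. No new recruitment is needed, provided siblings can be linked to a mother and infants to a site. The downside is imprecision. If the five original units were equal in size, each would hold 250 × 0.20 / 5 = 10 failures (20 in the merged unit). With 10 failures at AUC 0.80 the 95% half-width is about 1.96 × √(0.0850/10) = 0.18. The site results should therefore be read together as a check, and they may look worse than the 5-fold figure.

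### Stratified 5-fold cross-validation with about 5 to 10 failures per fold does not ensure a reliable sensitivity (identification rate) or a reliable variance for it

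*Protocol article*

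**What the plan says.** Under Statistical methods, Machine learning algorithms, the article plans stratified 5-fold cross-validation, "which ensures that reliable estimates of the sensitivity, specificity, and variance of the predictors can be obtained". Each infant goes into one subset, and the resulting ROC curves are used to choose the clinical trade-off between sensitivity and specificity. Repetition over further random partitions is not mentioned.

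Under Sample size, the starting point is an assumed failure prevalence of 20%. Then: "Using these values and an AUC precision of 0.1 led to an estimated sample size of 170 babies". That number is said to give "a minimum of 5 failure cases in each fold when performing 5-fold cross-validation", "thereby ensuring a reliable measurement of generalization power". The target was afterwards raised to 250 infants because of changing post-extubation support.

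Bootstrap methods appear twice: for the pilot-based variance in the sample size ("The variance in the AUC was then estimated by applying bootstrap methods to the data acquired in our pilot study") and for choosing the classification threshold. Neither use is described as supplying the variance of sensitivity or specificity.

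IR is defined as the number of failures placed in the FAILURE class divided by all failures. It is therefore the sensitivity for extubation failure at the high-confidence threshold.

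**The concern.** Both sentences are positive assurances, so later detail in an analysis plan would not make them true. Sensitivity rests on the failures alone, and each fold holds only a few. A variance read from five fold values is itself poorly determined, and the folds share training data, so the five values are not independent. The estimate also depends on which random partition was drawn.

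At stake is the development-stage performance claim and the operating point read from the ROC curves. An error bar from five folds could make IR look far better or far worse determined than it is.

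**Working it through.** **1. The plan's own figures.** 170 × 0.20 = 34 failures, or 6 to 7 per fold, so the stated minimum of 5 holds (down to a failure rate of 25/170 = 14.7%). At 250 infants, 250 × 0.20 = 50, or 10 per fold. A 10% failure rate would give 25, or 5 per fold.

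The 170 can also be reproduced with the binormal formula for the AUC, V = 0.0099·exp(−a²/2)·[(5a² + 8) + (a² + 8)/k], with a = 1.414·Φ⁻¹(AUC), k = 4 successes per failure and failures needed = 1.96²·V/0.1². The pilot variance is not given, so the AUC is assumed, and 0.1 is read as a 95% half-width:
- AUC 0.80: V = 0.085, 33 failures, 165 infants.
- AUC 0.775: V = 0.0895, 35 failures, 175 infants.

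Neither the fold count nor the sample size is wrong.

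**2. Sampling error of IR pooled over folds,** √[0.8 × 0.2/n]:
- n = 50: 0.057; 40/50 has an exact 95% interval of 0.66 to 0.90.
- n = 25: 0.080; 20/25 has an exact 95% interval of 0.59 to 0.93.

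**3. How well five folds estimate a variance.** With 4 degrees of freedom, the 95% limits on an SD are √(4/11.14) = 0.60 and √(4/0.484) = 2.87 times the estimate. Shared training data make even 4 generous.

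Drawing five binomial fold values at IR 0.8 and taking their SD divided by √5 gives:

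| Failures per fold | Binomial SE of pooled IR | Fold-based SE, 5th–95th percentile | Ratio |
|---|---|---|---|
| 5 | 0.080 | 0.040–0.120 | 3.0 |
| 7 | 0.068 | 0.029–0.105 | about 3.7 |
| 10 | 0.057 | 0.024–0.086 | about 3.5 |

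Shuffling a fixed 40/50 result into five folds of 10 already gives 0.032–0.084. These figures need no assumption about features or classifier.

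**4. Dependence on the partition.** This step needs assumed data: 40 features, 8 of them informative with mean shifts of 0.5, 0.7 or 0.9 SD, and a radial-kernel SVM on 17 features selected inside the training folds, with a fixed decision threshold. Each data set had 60 random stratified 5-fold splits; entries are medians over 12 data sets. The binomial SE is √[IR(1 − IR)/failures].

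| Failures / successes | IR | Split SD of IR | 95% width over splits | Binomial SE | Split SD of specificity |
|---|---|---|---|---|---|
| 50 / 200 | 0.74 | 0.040 | 0.140 | 0.062 | 0.023 |
| 50 / 200 | 0.85 | 0.030 | 0.105 | 0.050 | 0.018 |
| 50 / 200 | 0.90 | 0.023 | 0.080 | 0.042 | 0.014 |
| 34 / 136 | 0.68 | 0.053 | 0.185 | 0.080 | 0.030 |
| 34 / 136 | 0.82 | 0.040 | 0.140 | 0.066 | 0.022 |
| 34 / 136 | 0.87 | 0.030 | 0.111 | 0.058 | 0.017 |
| 25 / 225 | 0.56 | 0.068 | 0.250 | 0.099 | 0.020 |
| 25 / 225 | 0.69 | 0.065 | 0.231 | 0.092 | 0.016 |
| 25 / 225 | 0.78 | 0.049 | 0.180 | 0.083 | 0.012 |

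IR moves by 0.08 to 0.25 between splits of the same data. In every row the split SD is below the binomial SE. Specificity, with 27 to 45 successes per fold, has a split SD of 0.012 to 0.030. The 5th-to-95th percentile ratio of the fold-based SE is 2.9 to 3.5, in line with step 3.

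**5. Effect of repetition.** Averaging 20 splits reduces the 95% width for IR at 50 failures from 0.140 to 0.035 (IR 0.74) and from 0.105 to 0.026 (IR 0.85). At 25 failures it falls from 0.18–0.25 to 0.04–0.06. The sampling errors in step 2 are unchanged.

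**The case against.** **Single split and fold-based variance are inferred.** The article does not say that the procedure is run once or that the variance comes from five fold values. Repeats and interval methods are details that a full protocol or analysis plan could hold. This stands as a limit: the working applies to the text as written. It does not rescue the two assurances, which are tied to 5-fold cross-validation and to 5 failures per fold.

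**IR is pooled.** The article's IR uses all failures, so the relevant SE at 0.8 is 0.057, not the 0.126 of a single fold with 10 failures. This is right, and the comparison above uses the pooled value.

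**The split-to-split figures come from invented data.** Also right. They are a range under stated assumptions, and no single value is a property of the plan.

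**An independent check follows.** Fifty further infants are used only for evaluation, with the algorithm and parameters fixed in advance. A reader might infer that meeting IR 0.8 with FDR below 0.5 could turn on the cross-validation seed. The article does not support this: those objectives are set under Prospective APEX validation, and no partition enters that evaluation. The FAILURE-class threshold is assigned to bootstrap methods. The check is small, however: at 20% it has about 10 failures, and 8/10 has an exact 95% interval of 0.44 to 0.97. It can do little to correct a misjudged development estimate.

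**Conclusion.** The concern holds for sensitivity/IR and for its variance. With about 50 failures, stratified 5-fold cross-validation does not ensure that either is reliable. A fold-based SE of IR spans roughly threefold between its 5th and 95th percentiles, and this hardly depends on the classifier. The shift of about 0.08 to 0.25 in IR between splits does depend on the assumed data, the classifier and the number of failures.

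Three limits apply. Split noise is smaller than sampling error, so the small number of failures is the larger constraint. Specificity is clearly more stable, and a reader should not extend the criticism to it with equal force. Nor should a reader infer that the 170, the 250 or the fold count is miscalculated; they are consistent with the stated inputs. The consequence is confined to the development-stage estimate and the ROC trade-off drawn from it. The change should be made, but it does not call the design into question.

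**What to change.** - Repeat the stratified 5-fold procedure over many random partitions (for example 20 to 100), with feature selection and threshold choice inside the training folds each time. Report mean out-of-fold AUC, sensitivity/IR, specificity and FDR, with their spread over partitions.
- Take confidence intervals from an infant-level bootstrap that reruns the whole pipeline, not from the spread of five folds. Keep all copies of a resampled infant in the same fold, or evaluate on out-of-bag infants. Otherwise about 1 − exp(−0.8) = 55% of test records would have a copy in training, which would inflate performance and break the article's own rule against using one infant for both training and testing.
- In Machine learning algorithms and in Sample size, replace the two assurances with the precision that about 50 failures allow: an SE of about 0.06 for an IR of 0.8.

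The cost is computing time and intervals that may look less favourable. No further infants or data are needed. Repetition removes split noise only; the sampling error from few failures remains and should be reported as such.
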